### Secondary outcomes

Secondary outcomes include SOFA scores and multiorgan dysfunction score on days 1, 7 and 28 of hospital admission (if the patient is still an inpatient), mortality at 28 days, length of stay (LOS) in hospital, LOS in ICU, number of days of mechanical ventilation, thromboelastography parameters, arterial and venous blood gas parameters, and blood product requirements.

### Analysis of IDF video sequences

Prior to analysis, the recorded video sequences will be edited into at least three (and no more than five) video clips. All clips will be rated for quality using a five-point scale.^17^ Substandard images will be rejected. All IDF images will be analysed using a dedicated software tool (Automated Vascular Analysis V.3.02, Microvision Medical, The Netherlands). This is a semiautomated process which produces a number of data points from the video sequence. Analysis of the video clips will produce the following data:
Microvascular flow index;Total vessel density;Perfused vessel density;Proportion of perfused vesselsMicrocirculatory heterogeneity index.

This process is in accordance with recommendations made by an international consensus conference on assessing the microcirculation.^10^ Interobserver variation will be tested at regular intervals in order to minimise heterogeneity of data analysis between investigators. At the time of analysis, the investigators will be blinded with respect to the clinical time point of the study, the patients’ details, and the other outcome variables (SOFA score and haemodynamic data).

The following relationships will be examined:
Between microcirculatory parameters during the postresuscitation period and the development of SOFA scores;Between microcirculatory parameters and systemic haemodynamic data (stroke volume, cardiac output, blood pressure);Between microcirculatory parameters and plasma lactate and ScvO_2_ over the resuscitation period;Between microcirculatory parameters and coagulation parameters as assessed by ROTEM.

### Capacity and consent

This study complies with the Declaration of Helsinki, and will be conducted in accordance with the principals of Good Clinical Research Practice (GCP). In order to assess the response of the microcirculation to haemorrhagic shock and resuscitation, intubated and ventilated patients will be recruited to the study at an early stage following their admission to hospital, when capacity for informed consent will be absent.

Lack of patient capacity will be addressed by referring to the Mental Health Capacity Act (2005). In this situation, the physician in charge of the care of the patient (nominated consultee) will be consulted in order to consent on behalf of the patient. These physicians will have received prior briefing on the study protocol, and will not be a study investigator. If possible consent will also be sought from a personal consultee (the next of kin, relative or friend of the patient). When the patient regains capacity, the study will be explained and the participant asked for their consent to use the data collected so far, as well as any further samples required by the protocol. If the participant declines consent and wishes to be removed from the study, their data will be erased and no further samples will be collected.

Patients who die or who do not regain capacity within 28 days of injury will have their data entered into the study in accordance with the wishes of their personal or nominated consultee. This process is summarised in figure 2.

**Figure 2 BMJOPEN2015010893F2:**
[figure not shown]
Process flow chart.

### Confidentiality, data storage and security

All data relating to study participants will be treated in accordance with the Data Protection Act, 1998. All study data will be stored on a secure encrypted laptop used exclusively by the study investigators. Patients will be assigned an alphanumeric sequential study number that will be used to identify all clinical data. These numbers will be specific to each site. The patients’ demographic details will be linked to the study number on a separate screening database held on the secure computer at each site. Individual IDF image sequences will be assigned a random five-digit number. Identification of these video sequences will be achieved by cross-reference with an electronic database. On completion of the study, all participant identifying information and other study data will be securely archived in accordance with the policy of the sponsoring institution. All biological samples will be identifiable only by study number, and once analysis is complete the samples will be disposed off.

### Safety

The chief investigator has overall responsibility for the conduct of the study including responsibility for safety. Individual investigators will be responsible for reporting all serious adverse events (SAEs) and adverse events (AEs) to the chief investigator. There are no reported AEs associated with the use of IDF imaging in the published literature, and the risk of harm occurring to a study participant as a direct result of undergoing IDF imaging is close to zero. An example of an attributable AE would be a sublingual haematoma following IDF microscopy. SAEs will include death, any event which poses a threat to life, prolongs hospital stay or produces significant disability. Given the nature of the study population, it is anticipated that such features will be relatively common as part to the pathological process of trauma, but not as a result of participation in the study. The chief investigator will review all events to decide if there is any causal link. If this is the case action will be taken in accordance with the principals of ICH GCP.

### Statistical analysis

Normally distributed data will be presented as mean and SD, and non-normally distributed data will be presented as median and IQR. For comparison, patients will be dichotomised according to day 3 SOFA score into those with a score ≥6 versus those with SOFA score <6. The score of 6 has been chosen due to its prognostic relevance^18^ and previous utilisation as an end point for haemorrhagic trauma patients.^16^ Further analysis will be conducted according to the change in SOFA scores between days 1 and 3, so that patients are dichotomised into SOFA score ‘improvers’ and ‘non-improvers’. This approach has also been used as an end point for haemorrhagic trauma patients.^19^ Groups will be compared using a two-tailed t test for normally distributed data and the Mann-Whitney U test for non-normally distributed data. A p value of <0.05 will be considered statistically significant.

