**Methods and analysis:**

This multicentre prospective longitudinal observational study includes patients who present as an emergency with THS. Microcirculatory parameters are recorded using sublingual incident dark field microscopy alongside measurements of global flow (oesophageal Doppler and transthoracic echocardiography). Patients are enrolled into the study as soon as feasible after they arrive in hospital, and then at subsequent daily time points. Blood samples are taken for investigation into the mechanisms of microcirculatory dysfunction. Sequential Organ Failure Assessment scores will be analysed with microcirculatory parameters to determine whether they correlate with greater fidelity than more conventional, global circulatory parameters.

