### Number of patients

A single pilot study demonstrated feasibility in the examination of the microcirculation following THS, and reported data for 18 patients.^16^ The current study will be the first to examine the microcirculation of patients with THS as soon as they have arrived in the ED. The MICROSHOCK study will enrol 60 patients in order to further investigate the microcirculation following THS, and form hypotheses that might direct future goal-directed interventions.

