### Primary outcome

The primary outcome is the Sequential Organ Failure Assessment (SOFA) score at the D3 time point (72 h after admission to ICU), and will be recorded using information from the patients’ charts and laboratory results.

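### The primary outcome is the day-3 SOFA score, but the only analyses named for it cut the score into two groups, which costs a material share of the information from 60 patients

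*Protocol article*

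**What the plan says.** The Primary outcome section defines a score, not an event: "The primary outcome is the Sequential Organ Failure Assessment (SOFA) score at the D3 time point (72 h after admission to ICU").

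The abstract (Methods and analysis) says SOFA scores will be analysed with the microcirculatory parameters "to determine whether they correlate with greater fidelity than more conventional, global circulatory parameters". The section on analysis of the IDF video sequences also lists, without a method, the relationship between post-resuscitation microcirculatory parameters and how SOFA develops.

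Methods are named only in the Statistical analysis section, where "patients will be dichotomised according to day 3 SOFA score into those with a score ≥6 versus those with SOFA score <6". The reason follows: "The score of 6 has been chosen due to its prognostic relevance", together with its earlier use as an end point in haemorrhagic trauma. A further analysis classes patients by whether SOFA improved between days 1 and 3. For both splits, "Groups will be compared using a two-tailed t test for normally distributed data and the Mann-Whitney U test for non-normally distributed data", and "A p value of <0.05 will be considered statistically significant".

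On size, the Number of patients section says "The MICROSHOCK study will enrol 60 patients". It gives no power, effect size, standard deviation or expected share of patients with SOFA of 6 or more.

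**The concern.** The named analysis does not match the outcome it serves. After the cut, a patient scoring 5 and one scoring 6 count as opposites, while a patient scoring 6 and one scoring far higher count as the same. A two-group test then asks whether a parameter differs on average between the groups. It does not estimate how closely the parameter tracks organ dysfunction, which is what the abstract promises.

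The number of patients is fixed at 60 and no power statement shows that the study can afford to discard information. At stake is the power and precision of each association between a circulatory parameter and SOFA.

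**Working it through.** **Reproducing the plan's figure.** The 60 cannot be reproduced, because the article gives no inputs for it. For orientation, with 60 patients, two-sided alpha 0.05 and 80% power:

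- Full score, by the Fisher z approximation: detectable correlation = tanh[(1.96 + 0.84)/√57] ≈ 0.355.
- Two groups: detectable standardised difference = (1.96 + 0.84) × √(1/n1 + 1/n0), which is 0.72 at 50/50, 0.79 at 30/70 and 0.84 at 25/75.

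**Information lost by the cut.** Inputs: n = 60 and the cut at 6, both from the article. Assumptions: an approximately normal score, a linear analysis of the full score as comparator, and a share p of patients on one side of the cut. The article gives none of these three.

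Relative efficiency = φ(z)² / [p(1 − p)], where z is the normal quantile at p.

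- p = 0.50: 0.3989² / 0.25 = 0.637
- p = 0.25: 0.3178² / 0.1875 = 0.539
- p = 0.20: 0.2800² / 0.16 = 0.490

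| Assumed split | Efficiency | Loss | 60 patients act like |
|---|---|---|---|
| 50/50 | 0.637 | 36% | 38 |
| 40/60 | 0.622 | 38% | 37 |
| 30/70 | 0.576 | 42% | 35 |
| 25/75 | 0.539 | 46% | 32 |
| 20/80 | 0.490 | 51% | 29 |
| 10/90 | 0.342 | 66% | 21 |

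Under this model the smallest loss is about 36%, at an even split. The formula does not depend on the range of the score.

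**Power.** Assumptions: n = 60, a normally distributed parameter, a latent correlation of 0.35 (close to the 0.355 above), and a score rounded and limited to 0–24, cut at 6. The full-score and t-test results come from 20,000 runs with SD 4.

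| Share with SOFA ≥6 | Pearson, full score | Spearman, full score | t test after cut |
|---|---|---|---|
| 50% | 78% | 75% | 60% |
| 25% | 75% | 73% | 52% |
| 75% | 79% | 74% | 51% |
| 81% | 79% | 75% | 46% |

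The Mann-Whitney test, which the plan uses for non-normal data, was checked in two sets of 3,000 runs with SD 3.5. Power after the cut was 55–57% with half the patients at 6 or above, 53–55% with 35%, and 49% with 25%. Spearman on the full score gave 73–75% in the same settings.

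At 25–50% of patients with SOFA ≥6, the t-test shortfall against Spearman is therefore about 15 points (75 − 60) to 21 points (73 − 52). For Mann-Whitney it is about 18 points (75 − 57) to 24 points (73 − 49).

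**The case against.** **The cut is prespecified and reasoned.** This stands. The article gives both prognostic relevance and earlier use in the same kind of patient. The cited sources are not at hand, so the threshold cannot be called arbitrary. The reasons support reporting the comparison at 6. They do not explain why no named method uses the rest of the score.

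**Analysis of the score is intended.** A reader might infer that the study will never analyse the full score. The documents do not support that. The abstract speaks of correlation, the IDF analysis section lists relationships with SOFA, and the dichotomy is introduced as a comparison without being labelled the primary or sole analysis. The correlation method could also sit in a fuller plan that is not shown. What remains is that the section naming the methods names only two-group comparisons, so the outcome, the aim and the methods are out of step.

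**The size is conditional.** A reader might take a 36–46% loss as a property of this trial. It is not. It needs approximate normality, a linear comparator, and between 25% and 75% of patients at or above 6. Against a rank analysis the loss is somewhat smaller; with a more extreme split it is larger. The correlation of 0.35 and the SDs are also assumptions.

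**The study is hypothesis-forming.** The Number of patients section says so and claims no power, so no stated target is missed. This lowers the seriousness. However, the Primary objective asks whether microcirculatory parameters are better predictors than global ones, and avoidable loss of information still hurts an exploratory study.

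**Conclusion.** The point holds in this form: a graded primary outcome is paired with named analyses that only dichotomise it, and these do not deliver the stated correlation aim.

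Under a normal model with a linear comparator, the information loss is about 36% at best, 46% at 25/75 and 51% at 20/80. The actual split is not stated. At an assumed correlation of 0.35, with 25–50% of patients at 6 or above, power falls from 73–75% (Spearman) to about 52–60% (t test) or 49–57% (Mann-Whitney).

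A reader might extend these figures to the comparison of microcirculatory with global parameters. They do not cover it: only the association of a single parameter with SOFA was calculated. This is something the sponsor should change, not a flaw that invalidates the study.

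**What to change.** In the Statistical analysis section, state that the primary analysis is the association of each parameter with the full day-3 SOFA score, by Spearman correlation or a proportional-odds model. Keep ≥6 versus <6 as a prespecified secondary analysis, with its present rationale, for comparability with the earlier study.

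The cost is a change of wording; no new data or patients are needed. The small downside is that a correlation or odds ratio reads less directly at the bedside than a threshold, but the threshold result is still reported.

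Two matters lie outside this change. How deaths before day 3 enter the outcome is a question of outcome definition. Comparing the predictive strength of two kinds of parameter needs its own method, because a separate coefficient for each does not test the difference.

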**Trial registration number:**

NCT02111109; Pre-results.

Strengths and limitations of this study
This study's main strength is that it will be the largest clinical investigation into the microcirculatory response to traumatic injury and haemorrhagic shock to date.The MICROSHOCK study will recruit from major trauma centres in London and Birmingham, the two largest cities in the UK.The study is limited by its observational nature. However, the key research question ‘Does the microcirculatory behaviour predict outcome better than global haemodynamic parameters?’ can be addressed using observational data.A further limitation is the heterogeneous nature of injury patterns in the UK trauma patient population. Such differences will be addressed during data analysis, and reported during the dissemination of the results. These differences will be much greater than those in animal studies. However, a clinical study allows us to translate what has been learnt from animal research into useful and clinically relevant knowledge.

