### Primary objective

The primary objective of the MICROSHOCK study is to examine the microcirculatory function in patients following THS, and to determine whether these parameters are superior to global haemodynamic parameters in the prediction of clinical outcomes.

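### The primary objective asks whether microcirculatory parameters predict outcome better than global ones, but the tests named compare SOFA groups on each variable separately and cannot estimate that difference

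*Protocol article*

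**What the plan says.** The comparative question appears three times in the protocol article.

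- Primary objective: after examining microcirculatory function, the study is "to determine whether these parameters are superior to global haemodynamic parameters in the prediction of clinical outcomes".
- Strengths and limitations box: the key research question is "Does the microcirculatory behaviour predict outcome better than global haemodynamic parameters", and observational data are said to be able to address it.
- Abstract, Methods and analysis: SOFA scores will be analysed with microcirculatory parameters "to determine whether they correlate with greater fidelity than more conventional, global circulatory parameters".

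On the outcome, "The primary outcome is the Sequential Organ Failure Assessment (SOFA) score at the D3 time point". In Statistical analysis, "patients will be dichotomised according to day 3 SOFA score into those with a score ≥6 versus those with SOFA score <6", with a further split by change in SOFA between days 1 and 3. The inferential methods named there are: "Groups will be compared using a two-tailed t test for normally distributed data and the Mann-Whitney U test for non-normally distributed data", at p<0.05.

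The section Analysis of IDF video sequences lists four relationships to examine. They set microcirculatory parameters against SOFA, against systemic haemodynamic data, against lactate and ScvO2, and against ROTEM coagulation parameters.

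**The concern.** Superior prediction is a statement about a contrast: the predictive performance of a microcirculatory marker minus that of a global marker, in the same patients, for the same outcome. A two-sample test on one marker carries no information about that contrast. Running it once for each marker gives two separate answers and no estimate, standard error or test of the difference between them.

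At stake is the comparative half of the primary objective. If the Statistical analysis section is followed as it stands, the report can say which variables differ between patients with high and low day-3 SOFA. It cannot say whether microcirculatory imaging predicts better than cardiac output or blood pressure. Readers who want that answer would be tempted to take it from the pattern of p values, and a difference in significance is not a significant difference.

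**Working it through.** **1. Objective against analysis.** This step needs no numbers.

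| Place in the article | Links microcirculation to SOFA | Links global parameters to SOFA | Contrasts the two as predictors |
|---|---|---|---|
| Primary objective; Strengths and limitations | yes | yes | yes, as the question |
| Abstract, Methods and analysis | yes | yes | announced, no method named |
| Analysis of IDF video sequences, four relationships | yes (first item) | no | no |
| Statistical analysis | group test per variable | group test per variable, if applied | no |

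The second listed relationship, microcirculatory against systemic haemodynamic data, concerns whether the two move together. It is not a comparison of how well each predicts SOFA. That the tests are run one variable at a time is not written in the article; it follows from the two-sample tests named.

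**2. The plan's own figure.** The sample size is 60. It cannot be reproduced, because the article gives alpha (0.05, two-tailed) but no effect size, SD, power or expected SOFA split. Everything below except n = 60 and alpha is therefore an assumption.

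**3. What one group test can detect.** Detectable standardised difference at 80% power = (1.96 + 0.84) × √(1/n₁ + 1/n₂).

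- 30/30 split: 2.80 × √(1/30 + 1/30) = 0.72
- 18/42 split: 2.80 × √(1/18 + 1/42) = 0.79

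This is the precision of the planned test for a single marker. It says nothing about the contrast.

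**4. What side-by-side p values would do.** Assume two markers with the same true correlation with SOFA (0.25 to 0.45), correlated 0.3 with each other, and 30-50% of 60 patients with SOFA ≥6. By simulation:

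- exactly one marker has p<0.05 in about 26-44% of studies;
- the microcirculatory marker alone has p<0.05 in about 13-22%, which is half of the above by symmetry (26/2 = 13, 44/2 = 22).

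If the marker-SOFA correlation is raised to 0.6, the first figure falls to about 3-7%, because both tests are then nearly always significant.

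A second set of assumptions uses equal AUCs of 0.64 to 0.70, splits of 30/30 or 20/40, and correlation between markers of 0 to 0.5. It gives 21-51% for exactly one significant and 10-27% for the microcirculatory marker alone. In the same simulated studies, a direct paired test of the two AUCs (DeLong) rejects in about 4.5-6%, close to its nominal 5%.

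**5. What a direct comparison can resolve with 60 patients.** Under the first set of assumptions the SD of the paired AUC difference is 0.087 to 0.101. The 95% CI half-width is 1.96 × 0.087 = 0.17 to 1.96 × 0.101 = 0.20.

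Under the second set, the power of the paired test is:

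| True AUCs | Power |
|---|---|
| 0.75 vs 0.65 | about 18-30% |
| 0.80 vs 0.65 | about 34-61% |
| 0.80 vs 0.60 | about 52-83% |

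**The case against.** - **A comparison is announced.** The abstract commits to comparing how closely the two sets of parameters correlate with SOFA, and further relationships are listed under Analysis of IDF video sequences. This stands. A reader might infer that the group tests are the whole analysis and that superiority will never be tested. The article does not say so. It shows only that no method for the contrast is named.
- **No invalid rule is stated.** A reader might also infer that the investigators mean to declare superiority when the microcirculatory test is significant and the global one is not. That rule appears nowhere in the article, so the simulated rates describe a risk and not the plan.
- **This is a condensed article.** The full protocol or SAP may name a paired method. That holds for detail, but it does not remove the point: the article fixes an outcome split, tests and a significance level, and these do not match its own primary objective.
- **The study is hypothesis-forming.** The section Number of patients says so, and the first half of the objective, examining microcirculatory function, is served by the planned description. The comparative half is still presented as a question that the study can answer.
- **The Mann-Whitney statistic is close to what is needed.** U/(n₁n₂) is each marker's AUC. True; the missing piece is the paired difference and its uncertainty.
- **The simulation depends on its inputs.** It does, as the drop to about 3-7% at a correlation of 0.6 shows.

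**Conclusion.** The point holds as a mismatch between objective and analysis. The question is comparative, the tests named are not, and no section of the article supplies a method that contrasts microcirculatory with global parameters as predictors of SOFA. This conclusion rests on the text alone and on no assumed number.

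The rates of 26-44% and 13-22% illustrate why separate p values cannot stand in for the comparison. They apply to markers of modest strength with 60 patients and should not be read as the study's error rate. The article does not support a claim that an invalid superiority rule is planned, or that the comparison is certain to be left undone.

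**What to change.** In Statistical analysis, add a primary comparative analysis along these lines:

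> One microcirculatory parameter and one global haemodynamic parameter, both at one stated time point, are named before analysis. For day-3 SOFA ≥6 the primary estimate is the paired difference in AUC (microcirculatory minus global) in the same patients, with a 95% CI (DeLong). Superiority is concluded only if the CI excludes 0 in favour of the microcirculatory parameter.

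The investigators should choose the two parameters and the time point; the article gives no basis for choosing them here. There should be one estimand only, without a choice between correlation and AUC left open. Keep the t and Mann-Whitney tests as description. If a nested model is fitted (SOFA on the global parameter, then adding the microcirculatory one), report it as added value and not as superiority.

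If no direct comparison is to be made, reword the Primary objective and the key question in the Strengths and limitations box as exploratory association, in line with the hypothesis-forming aim under Number of patients.

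Cost: wording only and no new data, since both kinds of measurement are already collected. The real price is in the conclusion. With a half-width of about 0.17 to 0.20 in AUC, the comparison will often be inconclusive with 60 patients, and the report should say so.
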